### Data collection procedures

Data will be collected on all eligible trauma patients using standardized clinical chart abstraction of prehospital, in-hospital, and forensic pathology records. Probabilistic linking will be used to confirm patient identities from each site prior to entry into the research database. Abstracted data are entered into a research electronic data capture tool—REDCap [55, 56]. A team of research data collectors have been trained to collect data in a standardized process with all variables defined in a data dictionary. The overall study procedure is summarized in Fig. 2.

**Fig. 2 Fig2:**
[figure not shown]
EpiC data collection process

## Statistical methods

Descriptive statistics will be estimated for all demographic, injury, facility, clinical, and systems process fields. Multivariable models will adjust for characteristics at the patient-level (e.g., age, sex, race, comorbidities, socio-economic status, injury mechanism, injury severity index) and provider-level (e.g., specialist trauma surgeon, general medical officer, advanced prehospital provider), as described in Table 2. Due to the small number of hospitals, site will be adjusted for as a fixed effect.

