**Fig. 1 Fig1:**
[figure not shown]
Relative transport distances from EpiC study sites to the tertiary trauma care center (Tygerberg Hospital)

Tygerberg Hospital is the tertiary trauma (referral) center that provides specialty surgical and trauma care to a catchment area of 3.4 million people and attends to over 107,000 admissions annually of which 12,000–15,000 are seriously injured persons [35, 36]. All other EpiC hospital sites (Khayelitsha, Ceres, and Worcester Hospitals) refer complex and critical trauma patients to Tygerberg Hospital for a full range of trauma subspecialty care and consultations [37]. Khayelitsha Hospital is a frontline, district level facility that serves a dense urban catchment area of over 400,000 people and treats around 3,000 patients per month in the Emergency Center, many with injuries from interpersonal violence and motor vehicle collisions [38–40]. Worcester Hospital is a regional level facility that serves a rural population of 917,000 and can provide intensive care and general surgical care. Ceres Hospital is a rural, small district level facility without specialist physicians and offers basic trauma care. Patients at Ceres Hospital who require sub-specialty trauma and surgical care are stabilized and transferred to a trauma center by WCG EMS ambulances.

The WCG EMS is a public prehospital agency that annually treats and transports over 500,000 patients to hospitals, 40% due to trauma [41, 42]. Most ambulances are staffed by basic and intermediate life support providers, whereas advanced life support capable crews are reserved for the most critically injured patients [41, 42]. EpiC will include ambulances servicing catchment areas of the four participating hospitals. The Forensic Pathology Service (FPS) of the Western Cape has a constitutional mandate to perform autopsies on all unnatural deaths, including all trauma deaths. Two FPS labs will participate in this study: the Tygerberg FPS lab (includes deaths of patients from Tygerberg and Khayelitsha Hospital) and the Worcester FPS Lab (includes Worcester and Ceres Hospital deaths) [43].

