### Study design

This is a prospective, multicenter cohort study of trauma patients that will be conducted over a 6-year period, divided into 3 phases: a preparatory Phase 1 (year 1), a pilot implementation Phase 2 (year 2), and a main study Phase 3 (years 3–6).

***Phase 1. ***During the preparatory phase, we will create an evidence-based, expert-consensus data dictionary and data capture tools. This process will involve a review and adaptation of five international high-quality trauma data dictionaries (DOD Trauma Registry [44], National Emergency Medical Services Information System [45], National Trauma Data Standard [46], Pan-Asian Trauma Outcomes Study [47], and World Health Organization dataset for injury [48]), a scoping review of literature published in the past 10 years [49], and a modified Delphi consensus-building process using a panel of 20 military and civilian trauma clinical and research experts.

***Phase 2. ***We will conduct a pilot study at all study sites to assess the feasibility of implementation, data collection, and analysis. During this phase we will enroll ~ 1,000 patients with moderate and high acuity trauma (using the South Africa Triage Scale [SATS] acuity score), assess the frequency of erroneous and missing data, and conduct preliminary data analyses to describe the study cohort [50].

***Phase 3.*** In the main study, we will prospectively collect data from all study sites and perform statistical analyses to answer the research objectives.

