### Variables, outcomes, and study measures

Epidemiologic information will be collected for each study participant for their entire clinical course at all associated study sites, including: patient demographic information (e.g., age, sex, race, and comorbidities); injury details (e.g., time, type, and intent); facility data (e.g., hospital name, trauma level, clinician qualifications, units of care); clinical data (e.g., vital signs, medications administered, critical interventions, operations performed); and, trauma system process (e.g., key dates and times [51]). Table 2 describes the exposures, predictors, and outcomes of interest in the EpiC study.

**Table 2 Tab2:** Key EpiC Study Exposure, Predictors, and Outcome Measures

Exposures	Definition	Variable Type	Data Source
1^O—^Critical resuscitative interventions (CRI)	Prehospital and in-hospital resuscitative interventions or therapeutics, delivered for the patient’s traumatic injury (e.g., thoracostomy for tension pneumothorax), within the first 24 h post-injury	Binary	EMS and/or Hospital
1^O^—Trauma-to-CRI time	Duration of time from injury to receiving a critical resuscitative intervention for the dominant injury	Continuous	EMS, Hospital, and/or Pathology

Predictors	Definition	Variable Type	Data Source
Age	Span of years lived at the time of injury	Continuous	EMS, Hospital, or Pathology
Sex	Biological sex given at birth	Categorical	EMS, Hospital, or Pathology
Comorbidities	One or more pre-existing disease or conditions present in the patient that are trauma-relevant chronic conditions (e.g., bleeding disorder)	Binary	EMS or Hospital
Socioeconomic status	Based on hospital insurance status	Categorical	Hospital
Mechanism of injury	Main force that created the injury or how injury was inflicted (e.g., firearm, Struck/hit, stabbing or cut, vehicular injury, fall, thermal, choking/hanging, iatrogenic, other)	Categorical	EMS, Hospital, or Pathology
Provider level	Health care provider qualifications (e.g., rank of EMS provider, type of doctor)	Categorical	EMS
Injury severity	ISS calculated as the sum of squares of 3 worst AIS scores. Low (< 12) or high (≥ 12)	Continuous, Binary	EMS, Hospital, or Pathology

Outcomes	Definition	Variable Type	Data Source
1^O—^Ambulance death or 7-day in-hospital mortality	All-cause mortality in the ambulance or within the hospital in the first 7-days post-injury	Time-to-event	EMS, Hospital, or Pathology

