2^O^—30-day in-hospital mortality	All-cause mortality at any point during the hospital stay	Time-to-event	Hospital or Pathology
2^O^—Non-resuscitative surgical interventions	Post-injury interventional procedures such as fasciotomies, limb amputation, and laparotomies	Binary	Hospital
2^O^—Secondary infections	Post-injury infections such as wound infections, pneumonia, and sepsis	Binary	Hospital
2^O^—Organ failure	Organ failure will be assessed by individual organ (acute kidney injury, coagulopathy, and acute lung injury) and by a composite multiple organ failure score such the SOFA score up to 7-days	Continuous	Hospital

1^O^ = primary exposure or outcome; 2^O^ = secondary exposure or outcome; Data Source: EMS data is abstracted from WCG EMS Electronic Patient Care Reports, hospital data is abstracted from handwritten medical charts, and pathology data is abstracted from handwritten postmortem/autopsy reports from the Forensic Pathology Service of South Africa. EMS = Emergency Medical Services, ISS = Injury Severity Score, AIS = Abbreviated Injury Scale (anatomical score), SOFA = Sequential Organ Failure Assessment

The primary outcome of mortality will be defined as time to ambulance death or in-hospital death within 7 days of injury. The definition of examining mortality within 7 days was previously selected by a 20-person expert trauma panel to be the ideal duration to assess deaths for a study focused on the effects of early trauma resuscitation [52]. A study of three trauma-focused randomized controlled trials in urban U.S. settings have demonstrated that most hemorrhagic deaths occur in hospitals and within 6 h of patient encounter [51]. However, in our setting we examine a longer window since early deaths are more likely to occur at the scene due to the higher prevalence of penetrating injuries and fewer ambulance resources, and consequently later deaths will likely occur post-EMS transfer and hospital arrival. We will define the secondary outcomes of 24-h and 30-day mortality as time to in-ambulance or in-hospital mortality from injury. Other secondary outcomes include patients’ morbidity and need for operative interventions (those that are not considered damage control surgery), secondary infections (including wound infections, pneumonia, and sepsis), and organ failure (defined with the Sequential Organ Failure Assessment (SOFA) Score [53, 54]).

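### The named covariates measure severity only through the anatomical ISS and name no presenting physiology, leaving a serious risk of confounding by indication in the CRI effect

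*Protocol article*

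**What the plan says.** Under Statistical methods, the multivariable models adjust for characteristics at the "patient-level (e.g., age, sex, race, comorbidities, socio-economic status, injury mechanism, injury severity index") and for provider-level characteristics. Table 2 is cited for the description, and site enters as a fixed effect.

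Table 2 has one severity row: "ISS calculated as the sum of squares of 3 worst AIS scores. Low (< 12) or high (≥ 12"). Its variable type is given as both continuous and binary, and its source as EMS, hospital or pathology. The footnote adds: "AIS = Abbreviated Injury Scale (anatomical score").

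Three other statements bear on the point:

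- The variables section says that the study abstracts "clinical data (e.g., vital signs, medications administered, critical interventions, operations performed").
- The Phase 2 pilot enrols "patients with moderate and high acuity trauma (using the South Africa Triage Scale [SATS] acuity score").
- The Study setting section says that "advanced life support capable crews are reserved for the most critically injured patients".

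Neither vital signs nor triage acuity is named as a predictor. The Missing data section makes complete-case analysis primary and keeps multiple imputation of predictors for sensitivity analyses.

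**The concern.** The first objective is worded as the effect of CRI delivery and timeliness on 7-day mortality. The mortality analysis section says that the approach gives valid estimates of timeliness and effectiveness. That needs the main common causes of exposure and death to be in the model.

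A CRI is given for acute compromise; Table 2's own example is a thoracostomy for tension pneumothorax. Two patients with the same ISS can differ greatly in blood pressure, breathing and consciousness. The one in worse condition is likelier to be treated, to be treated early, and to die. This bias runs against the stated hypothesis that missing or late CRI raises mortality. A null or reversed result from the named covariates would therefore be hard to interpret.

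No other stated method deals with this. A time-dependent CRI term handles immortal time. Left truncation, joint modelling and the survivor average causal effect are to be considered only as necessary, and they address timing and truncation by death. The Limitations section does not mention confounding by indication.

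A smaller, related issue is the ISS source. Table 2 permits pathology as a source, and autopsy findings exist only for patients who died. Without a source rule, the one severity covariate could be measured differently by outcome.

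**Working it through.** **1. The plan's own figure.** Inputs from the Power calculation section: 14,400 cases, 30% with CRI within 2 h, 10% 7-day mortality, two-sided alpha 0.05, 80% power, detectable HR 0.85.

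- Events: 14,400 × 0.10 = 1,440.
- Events needed (Schoenfeld): (1.960 + 0.842)² / [0.30 × 0.70 × (ln 0.85)²] = 1,416, or 14,160 cases.
- Power with 1,440 events: 80.7%.
- Detectable HR: exp[−2.802 / √(1,440 × 0.21)] = 0.851.

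The stated 0.85 reproduces. It does not depend on the covariate list and is not in dispute.

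**2. How much bias cancels the target.** 1 / 0.85 = 1.18. Residual confounding by a factor of about 1.18 against early CRI brings a true 0.85 to 1.

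**3. What an unadjusted physiological marker could do.** The documents give neither the prevalence of deranged first vital signs nor their hazard ratio, so all inputs here are assumptions. Let h be the mortality HR of the marker, given the covariates already in the model. Let p1 and p0 be its prevalence with CRI within 2 h and otherwise. Then

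bias factor = [1 + (h − 1)p1] / [1 + (h − 1)p0], and apparent HR = 0.85 × bias factor.

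This is the usual external-adjustment approximation for a binary confounder with no interaction.

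| p1 vs p0 | h = 2: factor, apparent HR | h = 3: factor, apparent HR | h = 5: factor, apparent HR |
|---|---|---|---|
| 20% vs 15% | 1.043, 0.887 | 1.077, 0.915 | 1.125, 0.956 |
| 30% vs 20% | 1.083, 0.921 | 1.143, 0.971 | 1.222, 1.039 |
| 40% vs 20% | 1.167, 0.992 | 1.286, 1.093 | 1.444, 1.228 |
| 50% vs 20% | 1.250, 1.062 | 1.429, 1.214 | 1.667, 1.417 |

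Worked cell (h = 3, 40% vs 20%): (1 + 2 × 0.40) / (1 + 2 × 0.20) = 1.8 / 1.4 = 1.286, and 0.85 × 1.286 = 1.093.

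Six of the twelve cells stay below 1 and six exceed it. In the mildest cell, ln 1.043 / |ln 0.85| = 0.042 / 0.163, so about a quarter of the log hazard ratio is lost.

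**4. What adjustment costs in precision.** If the added covariates explain a share R² of the exposure (assumed), effective events are 1,440 × (1 − R²).

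| R² | Power at HR 0.85 | Detectable HR |
|---|---|---|
| 0 | 80.7% | 0.851 |
| 0.05 | 78.7% | 0.848 |
| 0.10 | 76.5% | 0.844 |
| 0.20 | 71.5% | 0.835 |
| 0.30 | 65.7% | 0.825 |

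**The case against.** The strongest reply is that the article does not close its covariate list. The patient-level covariates are given as examples, Table 2 is headed as key measures, and race is in the text but not in the table. A full analysis plan may name vital signs. This stands: a reader might infer that the plan excludes physiology, but the documents show only that it is not named. The point survives because a table of key predictors that includes insurance status but no first blood pressure or consciousness level leaves a central confounder to discretion.

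ISS is also not the only covariate carrying acuity information. Provider level is in the models and, since advanced crews go to the most critically injured, it is a partial proxy. Mechanism and site add something. This also stands, and it would lower the bias, but none of these measures the patient's condition at presentation.

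Three further readings are tempting and go beyond the text:

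- That the main study uses SATS acuity and then ignores it. SATS appears once, for pilot enrolment; whether the main study records it has to be confirmed.
- That patients who died in hospital will have ISS scored at autopsy. Pathology is listed as a possible source, as it is for age, sex and mechanism. Differential measurement is possible, not stated.
- That ISS will be used only as a split at 12. Table 2 already lists it as continuous as well.

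Finally, adding vital signs is not free. With complete-case analysis as primary and handwritten hospital charts as a source, each added item could remove patients.

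**Conclusion.** The concern holds as a serious risk of residual confounding by indication in the primary CRI estimate. The named set contains no presenting physiology although vital signs are already collected, and no stated method or limitation covers the gap. Because the target effect is only HR 0.85, modest residual confounding is enough to shrink, cancel or reverse it. Under the assumed prevalences and hazard ratios the factor is 1.04 to 1.67, giving an apparent HR of 0.89 to 1.42.

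A reader might infer that early CRI is bound to look harmful, or that the primary question cannot be answered. The documents do not support that. They give no inputs from which to compute the bias, the milder scenarios still show a protective HR, and the scenarios make no explicit allowance for what provider level, mechanism and site absorb. The power calculation is not wrong on this point.

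**What to change.** 1. Add the first recorded pre-CRI systolic blood pressure, heart rate, respiratory rate and, where recorded, consciousness level to the Table 2 predictors and the primary models. Add SATS if the main study records it. Restrict to values taken before CRI, since later ones may be affected by it. Model them flexibly, with ISS in its continuous form.
2. Make multiple imputation of missing predictors part of the primary analysis and move complete-case to sensitivity. Without this change, step 1 would drop patients.
3. State an ISS source rule that does not depend on outcome: for patients who reached hospital, score from EMS and hospital records, with autopsy-based scores as a sensitivity analysis.
4. List residual confounding by indication under Limitations.

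The cost is mainly analysis-plan wording, since vital signs are already abstracted. The downsides are some missing vital signs and the precision loss shown above: power at HR 0.85 of about 79% to 66%, against 80.7%, if the added covariates explain 5% to 30% of exposure (assumed).

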### Participant recruitment and informed consent

Eligible patients will be identified daily at all study sites. The clinical records of patients meeting inclusion criteria will be reviewed and data will be abstracted into the study database. Data for each patient will be linked as they traverse the emergency care system. Consistent with other observational emergency care studies, a waiver of informed consent was approved by the ethics boards to practically carry out this minimal risk research on patients with emergent (i.e., time-sensitive, and life-threatening) conditions.

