### Assessing association with mortality outcomes

Time-to-event analyses will be used to estimate the association between delivery and trauma-to-CRI time with mortality outcomes. This approach allows us to (1) systematically follow a representative cohort of injured individuals that are alive at the initial request for medical attention with moderate to high baseline risks, and (2) produce valid estimates of the timeliness and effectiveness of the urgent care initiated within the regional trauma system for these individuals [57]. Multivariable Cox proportional hazards models with a time-dependent covariate for CRI will be used to study the effect of receiving CRI during different time periods post-injury (e.g., 0–2, 2–12, > 12 h). We will assess model fit and the proportional hazards assumption. We will consider alternative model specifications as necessary, including a left truncated Cox proportional hazards model [58, 59], joint modelling of CRI and death [60–62], and estimating the survivor average causal effect (SACE) [63–66].

The secondary objective of assessing the effect of the delivery and timing of individual resuscitative interventions that occur during clinical course will be evaluated using similar models. Some interventions are injury-specific, and thus analysis will be performed in appropriate subgroups (e.g., by injury type and injury severity).

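### Site as a single fixed effect in the Cox models can distort the CRI-timing hazard ratios if hospitals differ in both CRI timing and death timing; stratifying the baseline hazard by site avoids this at almost no cost

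*Protocol article*

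**What the plan says.** Under Statistical methods, the protocol article states for its multivariable models: "Due to the small number of hospitals, site will be adjusted for as a fixed effect".

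Under Assessing association with mortality outcomes, the chosen approach is "Multivariable Cox proportional hazards models with a time-dependent covariate for CRI". The timing question is put in terms of periods after injury, with 0–2, 2–12 and >12 h as examples. The same paragraph adds: "We will assess model fit and the proportional hazards assumption". It then leaves room for other specifications and names three as examples: a left-truncated Cox model, joint modelling of CRI and death, and the survivor average causal effect.

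Under Study setting, Table 1 lists four hospitals: a 1,384-bed trauma centre, an urban district hospital, a rural regional hospital, and a 28-bed rural district hospital 125.5 km from the trauma centre. The three others "refer complex and critical trauma patients to Tygerberg Hospital". Patients at the smallest who need sub-specialty care "are stabilized and transferred to a trauma center by WCG EMS ambulances". Under Participant recruitment and informed consent: "Data for each patient will be linked as they traverse the emergency care system". The article does not say which hospital counts as the site of a transferred patient.

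**The concern.** With hospital indicators, the model is λ(t) = λ0(t)·exp(γ_site + β·CRI(t) + other covariates). Each hospital's hazard is then a fixed multiple of the others at every hour after injury. If one hospital's deaths come early and another's come late, one multiplier cannot describe both.

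The lack of fit matters because CRI is itself a function of time. Person-time after late CRI lies late in follow-up and, if hospitals differ in how quickly they deliver CRI, comes mostly from the slower hospitals. Hour-by-hour differences between hospitals that γ_site cannot absorb can then load onto the CRI-period coefficients.

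Timeliness of CRI is part of the first objective, and these coefficients are where it is read. The stated reason, few hospitals, explains fixed rather than random effects. It gives no reason to prefer indicators to strata.

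**Working it through.** **1. The protocol's own figure.** Inputs from Power calculation: N = 14,400, 10% 7-day mortality, 30% with CRI within 2 h, two-sided alpha 0.05, 80% power, HR 0.85.
- Expected deaths: 14,400 × 0.10 = 1,440.
- Deaths needed (Schoenfeld): (1.960 + 0.842)² / (0.30 × 0.70 × (ln 0.85)²) = 7.85 / (0.21 × 0.02641) ≈ 1,416, or N = 14,160.
- With 1,440 deaths, power is 80.7% and the detectable HR is exp(−2.802/√(0.21 × 1,440)) = 0.851. The figure reproduces.

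**2. Can strata be supported?** 1,440 / 4 = 360 expected deaths per hospital, using the protocol's average of 3,600 cases each. Two comparisons of standard errors under strata and indicators gave 0.071 against 0.071, and 0.148 against 0.149.

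**3. Simulation with no CRI effect.** From the protocol: four hospitals of 3,600, about 1,440 deaths in 7 days, about 30% with CRI within 2 h, and the three example periods. Assumed: CRI mix by hospital (20–45% at 0–2 h, 10–25% at >12 h), mortality of 8–13% by hospital, and the median death times below. There were 300 replicates per scenario, and the comparator is not yet treated.

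| Scenario (median hours to death at the four hospitals) | HR with site indicators, CRI at 0–2 / 2–12 / >12 h | False positives |
|---|---|---|
| Same death timing, CRI mix differs | 1.00 / 1.00 / 1.00 | 7 / 6 / 3% |
| Death timing differs, same CRI mix | 1.00 / 1.00 / 1.00 | 3 / 5 / 6% |
| Both differ, mild (48/24/24/36) | 1.02 / 1.03 / 1.06 | 6 / 8 / 9% |
| Both differ, moderate (48/12/12/24) | 1.04 / 1.07 / 1.15 | 7 / 14 / 30% |
| Both differ, strong (72/6/6/24) | 1.05 / 1.13 / 1.29 | 10 / 37 / 70% |
| Both differ, reversed (12/48/48/24) | 0.97 / 0.95 / 0.88 | 9 / 8 / 21% |

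Stratified by site, every HR lay between 0.996 and 1.006, with false positives of 3–7%. Monte Carlo error on these rates is about 1–3 points.

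**4. Size against the target effect.** The false early-to-late ratio (0–2 h over >12 h) is 0.96 (mild), 0.90 (moderate), 0.82 (strong) and 1.10 (reversed). On the log scale, with |ln 0.85| = 0.163, these are 0.040/0.163 = 24%, 0.102/0.163 = 63%, 0.201/0.163 = 124%, and 0.097/0.163 = 60% in the opposite direction. For single periods, 1.15 is close to 1/0.85 = 1.18 and 1.29 is beyond it. The powered contrast (within 2 h versus not) is not identical to these, so the comparison is one of scale.

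A smaller null simulation (30 replicates; assumed CRI medians of 1.5 h urban and 5 h rural; Weibull shapes 0.40/0.60 and 0.35/0.70) gave late-to-early ratios of 1.15 and 1.26 with indicators and 1.01 with strata.

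**5. Would the planned check see it?** A likelihood-ratio test of site × log(time) rejected in all of the first 100 datasets of every scenario in which death timing differed.

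**6. Transfers, examined separately.** Assumed: 30% of patients at the three referring hospitals move 3–12 h after injury, 60% of these have CRI only after arrival, and the hazard at the trauma centre is 1.25, 1.5 or 2 times that elsewhere (150 replicates, CRI null).
- First-site coding, indicators: HR for CRI at 2–12 h of 1.05 / 1.08 / 1.14.
- First-site coding, strata: 1.04 / 1.07 / 1.13, so stratifying does not remove it.
- Time-varying current site: 1.00 / 1.00 / 1.00.
- The site test under first-site coding rejects in only 8 / 12 / 24% of datasets.

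Coding by final hospital, in a separate run (about 17% transferred, 16 replicates, Monte Carlo SE on the log HR up to 0.04), gave 1.14 / 1.09 / 0.98 for the three periods.

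**The case against.** The strongest reply is that the protocol already plans to check proportional hazards and keeps its list of alternatives open. Non-proportional site effects are what such a check finds, and with about 1,440 deaths a test that included site would almost certainly find them. This largely stands: it makes an undetected error from differing death timing unlikely. What remains is that site is not named in the check and site strata are not among the named alternatives, so the remedy would be picked after the data are seen.

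Second, the bias needs both CRI timing and death timing to differ by hospital, and the protocol documents neither. That stands too. A reader might infer from the range of facilities that the hospitals do differ and that the timing results will be biased. The document supports only that they may. Mild differences do little, and the sign is not fixed.

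Third, a fixed effect for site could be read loosely enough to allow strata. The usual reading in a Cox model is indicators, but one added sentence would settle it.

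On transfers, a reader might infer that site means the hospital of final care, or that only the first hospital may ever be used. The protocol says neither. Coding rules may well sit in the data dictionary or an analysis plan that is not shown, and the simulations count against a ban on current-site coding. They do not prove current-site coding correct either: simulated transfers were unrelated to prognosis, whereas the protocol says the sicker patients are referred.

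**Conclusion.** The concern holds as a choice of method that can be improved. It is not a demonstrated error in the results to come. Site indicators in a Cox model with time-dependent CRI can create a timing gradient under a null effect when CRI timing and death timing both vary by hospital. The size runs from negligible (1.02/1.03/1.06) to comparable with or beyond the effect the study is powered for (1.04/1.07/1.15 up to 1.05/1.13/1.29), in either direction. All inputs by hospital are assumptions. If either timing is the same across hospitals, there is no bias. Strata removed it in every death-timing scenario with essentially no loss of precision, so there is little reason to wait for a failed check.

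The coding of site for transferred patients is a secondary clarification. Strata do not solve it, and the proportional hazards check often misses it.

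**What to change.** Under Statistical methods, state that the Cox models stratify the baseline hazard by site, giving four strata of about 360 expected deaths each, and that site stays a fixed effect in the GLMs. Under Assessing association with mortality outcomes, state that site is included in the proportional hazards assessment of any unstratified model.

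As a clarification, add one sentence on coding: site is the first study hospital reached or, for deaths before hospital arrival, the hospital whose catchment the ambulance serves. The final hospital is not used as a baseline covariate. Time-varying current site is reported as a sensitivity analysis. Current-site coding should not be ruled out, because first-site strata alone leave bias when the hazard changes on transfer.

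The cost is a few sentences and one model option, using data already being collected and linked. No site hazard ratio would be estimated, but none is an objective.
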